## Abstract

**Background:**

Chronic kidney disease (CKD) is public health concern even in Asian countries. TRK-100STP, a sustained release tablet of an orally-active prostacyclin analogue, beraprost sodium, is suggested to suppress worsening of some parameters of renal filtration function, containing in slope of 1/serum creatinine (1/SCr) vs. time in a phase II clinical trial.

**Methods/design:**

We describe the design of the phase IIb/III trial of TRK-100STP, CASSIOPEIR (**C**RF **As**ian **S**tudy w**i**th **O**ral **P**GI_2_ derivative for **E**valuating **I**mprovement of **R**enal function) conducted in approximately 160 centers in China, Hong Kong, Japan, Malaysia, Republic of Korea, Taiwan, and Thailand. A total of 750 patients (n = 250 per group) with primary glomerular disease or nephrosclerosis were planned to be enrolled. Patients were randomized into one of three treatment groups in a double-bind, placebo-controlled manner: TRK-100STP 60 μg b.i.d.; TRK-100STP 120 μg b.i.d.; or placebo. The treatment period is planned to last 2 to 4 years. The primary efficacy endpoint is the renal composite endpoint including doubling of SCr and ESRD (dialysis induction, renal transplantation, or increase in SCr to ≥6.0 mg/dL).

**Discussion:**

This trial targeting CKD patients is designed to (a) demonstrate the superiority of TRK-100STP over placebo using renal composite endpoints, (b) determine the recommended clinical dose, and (c) assess the safety of TRK-100STP in this population and setting.

**Trial registration:**

ClinicalTrials.gov Identifier: NCT01090037.

**Electronic supplementary material:**

The online version of this article (doi:10.1186/1471-2369-15-153) contains supplementary material, which is available to authorized users.

## Background

The number of patients with end-stage renal disease (ESRD) requiring dialysis or renal transplantation has increased globally in recent years. Among the primary diseases that lead to ESRD are the primary and secondary glomerular diseases such as diabetic nephropathy and tubulointerstitial nephritis.

Primary glomerular diseases and nephrosclerosis still comprise a significant proportion of chronic kidney disease (CKD) patients. Primary glomerular diseases are especially important causes for the need for dialysis in Asian countries. They are currently the most frequent causes in China
[1] and the second in most other Asian countries
[2–4]. Nephrosclerosis is the third frequent cause in most Asian countries and has been increasing
[1–5].

The primary care of CKD treatment is to delay renal function deterioration. Current treatments include dietary restriction and antihypertensive drug therapy. Angiotensin-converting enzyme inhibitors (ACEIs) and angiotensin-II receptor blockers (ARBs), which are often administered to both diabetic nephropathy and non-diabetic CKD patients, have been established as the recommended treatment agents for non-diabetic nephropathy patients
[6], although either ACEIs or ARBs are insufficient for the prevention of progressive renal disease. Therefore, an additional treatment that is able to significantly delay the progression of CKD is highly coveted.

To meet this unmet medical need, clinical trials have been conducted attempting to delay CKD progression with combination therapies using renin-angiotensin system (RAS) inhibitors. Unfortunately, these trials failed to show an improvement in efficacy with composite renal endpoints while adverse events increase in some of them. Clinical benefits of combination treatments with multiple RAS inhibitors are therefore unproven, at least for diabetic nephropathy
[7–10].

Furthermore, a recent trial of Nrf2-activating bardoxolone methyl in diabetic nephropathy patients (BEACON) was prematurely terminated due to safety concerns
[11]. A trial of an orally administered activated carbon preparation (AST120: Kremezin®), which is currently used in clinical practice for chronic renal failure in Japan, Republic of Korea and Taiwan, also failed to meet the efficacy endpoints in composite renal endpoint in the large EPPIC randomized controlled trials
[12]. The development of a novel CKD treatment strategy is therefore increasingly needed.

Beraprost sodium (BPS) is a stable orally-active prostacyclin (PGI_2_) analogue discovered by Toray Industries, Inc. to overcome instability of prostacyclin *in vivo*
[13]. BPS has a novel mechanism for suppressing the progression of CKD. This treatment also targets renal hypoxia, reflecting a growing body of evidence implicating this as a valid therapeutic approach
[14]. BPS has been found to be effective in various animal models of renal disorders
[15–19]. In addition, BPS immediate-release tablets prevented the decrease in renal blood flow and function in patients with chronic renal failure
[20, 21].

Using sustained release tablets of BPS (TRK-100STP), a randomized double-blind placebo-controlled comparative phase II trial aiming to determine the optimal clinical dose was conducted from 2005 to 2008 in Japanese patients with primary glomerular disease or nephrosclerosis as the primary disease
[22]. In this trial, serum creatinine (SCr) values were 1.5 to 4.5 for male and 1.3 to 4.0 for female at the initiation of treatment. Randomized patients received oral TRK-100STP 120 μg/day (60 μg b.i.d.), 240 μg/day (120 μg b.i.d.) or placebo for 28 weeks after the 22-week run-in period. The primary endpoint was the difference in slope of 1/SCr vs. time between the run-in period and the treatment period. No statistical difference in the primary endpoint was found between the high-dose (240 μg) group and the placebo group and so a clinical dose recommendation was not determined. Both treatment groups showed better outcomes than the placebo group, with the low-dose (120 μg/day) group showing the highest efficacy. Both active dose groups showed similar effectiveness for additional efficacy endpoints including creatinine clearance, SCr ratio and serum cystatin C, compared to those of the placebo group.

A subgroup analysis was also conducted in the same study among patients with SCr 2.0 mg/dL or higher, whose renal function deterioration was considered irreversible
[23]. Deteriorations in all the representative renal filtration functions (i.e. difference in the slope of the 1/SCr vs. time between the run-in period and the treatment period, SCr ratio, serum cystatin C and eGFR) were suppressed in the treatment groups and significant suppressions have been observed in some of these parameters. On the other hand, no clinically relevant safety issues were observed.

Based on these results, it was judged that a hypothesis could be set up to be verified in the phase IIb/III trial. The clinically recommended dose is to be re-evaluated using the same doses as ones in the phase II trial.

This paper details the design and methodology of a phase IIb/III trial (CASSIOPEIR: **C**RF **As**ian **S**tudy w**i**th **O**ral **P**GI_2_ derivative for **E**valuating **I**mprovement of **R**enal function) conceived on the basis of the evidence and findings mentioned above in order to investigate whether TRK-100STP is superior to placebo in treating patients with primary glomerular disease or nephrosclerosis. Evaluating composite renal endpoints, the trial aims also to determine a recommended therapeutic dose of TRK-100STP.

## Methods/design

### Aim of trial

This is a multicenter, randomized, double-blind, placebo-controlled, parallel-group comparative trial targeting CKD patients designed to: (a) demonstrate the superiority of TRK-100STP over placebo using renal composite endpoints, including the extension of the time to the start of dialysis treatment; (b) determine the recommended clinical dose by comparing the low-dose (120 μg/day), high-dose (240 μg/day), and placebo groups; and (c) assess the safety of TRK-100STP in this population and setting.

### Study design

The trial is being conducted in approximately 160 sites, including centers in China, Hong Kong, Japan, Malaysia, Republic of Korea, Taiwan and Thailand. The protocol has been approved by the Ethics Review Committee/Institutional Review Board affiliated with each center. The trial is being conducted in accordance with Good Clinical Practice, and Declaration of Helsinki. All patients provided written informed consent. The trial has been registered on ClinicalTrials.gov, NCT01090037.

A total of 750 patients (n = 250 per group) with primary glomerular disease or nephrosclerosis are planned to be randomized. The rationale for setting the sample size at 250 subjects per group is based on “data handling procedure #2: 3-month lag censoring analysis” as follows. In the event of doubling of SCr or increase in SCr to ≥6.0 mg/dL, the 2.5-year event rate estimated from subjects with SCr ≥2.0 mg/dL that were enrolled in the last phase II trial was 48% for the placebo group and 33% for 240 μg group. Therefore, assuming a 2-year-enrollment period, a 2-year follow-up period, and a 35% dropout rate at 2.5 years for each group, the number of subjects required per group is estimated at 237 (with two-sided 5% significance level and 90% statistical power). For all subjects, placebo was orally administered for 2 to 8 weeks, twice a day, during the run-in period, when subjects were blinded although investigators recognized that subjects received placebo (Figure 
1). Prohibited and restricted concomitant medications are detailed in Table 
1. Subjects who met the inclusion and exclusion criteria (summarized in Table S2; see Additional file
1) after 2-to-8-week run-in period were randomized into one of three treatment groups for the 2-to-4-year treatment period in a double-bind manner: TRK-100STP 120 μg; TRK-100STP 240 μg; or placebo. Subjects randomized in the 240 μg dose group started with a daily dose of 120 μg for 2 weeks and was then increased to 240 μg/day. While the treatment period was planned to last for 2 to 4 years, this may be extended if the incidence of renal composite endpoint is smaller than expected.

**Figure 1 Fig1:**
[figure not shown]
**Schematic diagram of the CRF Asian Study with Oral PGI**
_**2**_
**derivative for Evaluating Improvement of Renal function (CASSIOPEIR) study design.**

**Table 1 Tab1:** **Prohibited and restricted concomitant medications**

Prohibited Concomitant Medications	The following medications are prohibited for use during the study period.
	(1) Prostaglandin drugs except for ophthalmic solutions and ointments.
	(2) Fluorinated pyrimidine antifungal agents.
Restricted Concomitant Medications	(1) For ACEIs and ARBs, changing the dose or introducing the medication is not permitted from the obtaining of informed consent to the end of the study drug administration. Antihypertensive drugs other than ACEIs or ARBs are permitted to be used.
	(2) From obtaining of informed consent to the end of the study drug administration, changing the dose or introducing the medication is not permitted for pentoxifylline, dilazep hydrochloride, or dipyridamole.
	(3) From obtaining of informed consent to the end of the study drug administration, NSAIDs are not permitted to be taken for more than four consecutive weeks; and during the week prior to a visit, NSAIDs are not permitted to be taken.

### Study endpoints

The primary efficacy endpoint for the trial is the renal composite endpoint (time to first occurrence of one of the following events): 1) Doubling of SCr; defined as at least a two-fold increase in SCr during the treatment period over the baseline value during the run-in period (mean value of the last two measurement results during the run-in period); and 2) ESRD (occurrence of any of the following: introduction of dialysis, renal transplantation, or increase in SCr to ≥6.0 mg/dL). With regards to the doubling of SCr, and the increase in SCr to ≥6.0 mg/dL, a re-confirmation will be performed with blood sample collection and measurement four or more weeks after the initial date on which these endpoints were confirmed, and once reconfirmed, the initial date will be judged as the date on which these renal composite endpoints are reached. The clinical trial and administration of the study drug will be continued for the subject even after the confirmation that SCr has doubled or increased to ≥6.0 mg/dL until introduction of dialysis or renal transplantation is deemed necessary. If the administration of the study drug is prematurely discontinued during the treatment period, the clinical study will be continued as an efficacy follow-up until introduction of dialysis or renal transplantation is judged to be needed.

Secondary endpoints are as follows: 1) Renal composite endpoint or death (from any causes); 2) doubling of SCr; 3) ESRD; 4) introduction of dialysis; 5) renal transplantation; 6) increase in SCr to ≥6.0 mg/dL; 7) slope of 1/SCr vs. time; and 8) eGFR. In addition, the safety endpoints include adverse events, laboratory tests, vital signs and body weight, and 12-lead electrocardiogram (ECG). Also to be evaluated are miscellaneous efficacy endpoints such as “cardiovascular events or renal composite endpoints”.

All SCr values used for analysis of the endpoints are measured at the central clinical laboratory.

### Analysis set

The full analysis set (FAS) will consist of subjects taking at least one dose of study drug for the treatment period. However, subjects meeting the following descriptions are excluded from the FAS:Subjects providing no data after administration of the study drug for the treatment period;Subjects found not to fulfill the inclusion criterion (2) or (3);Subjects found to meet the exclusion criterion (1), (2), or (6).

Subjects who satisfy all of the following criteria out of FAS constitute the per protocol set (PPS), and are:Subjects meeting the inclusion criteria;Subjects not meeting the exclusion criteria;Subjects providing three or more SCr measurement data points obtained at and after Week 4 of the treatment period (including at least one data point taken at Day 70 of the treatment period or later);Subjects whose drug compliance rate is two-thirds or higher during the administration period of the study drug for the treatment period.

The safety analysis set (SAF) will include subjects taking at least one dose of the study drug for the treatment period.

The pharmacokinetics analysis set (PKAS) is defined by subjects fulfilling all of the following criteria:Subjects taking at least one dose of the study drug for the treatment period;Subjects providing at least one data point (sample) for plasma BPS concentration determination for which information on the date and time of blood collection and medication before the collection is available.

### Handling of data

For efficacy assessment, the following three types of data handling processes have been established:Data Handling Procedure #1All data will be adopted for analysis that is obtained after the start of the administration of the study drug for the treatment period (Intension-To-Treat (ITT) analysis).Data Handling Procedure #2For subjects who discontinue the administration of the study drug for the treatment period, their data obtained after 3 months following the discontinuation will not be used, and data collection for them is censored at 3 months from the discontinuation or at completion of the study, whichever comes first (3-month lag censoring analysis).Data Handling Procedure #3Subjects that take a prohibited concomitant medication will be censored at the time of the medication. Subjects will be censored at any time when they stop taking the study drug for the treatment period, for whatever reason.

### Analysis of efficacy

The primary population for efficacy analysis will be the FAS, and the data will be processed according to the Data Handling Procedure #1. Similar analyses will be conducted according to the Data Handling Procedure #2 in terms of FAS and according to the Data Handling Procedure #3 in terms of PPS. Statistical testing will use two-sided 5% significance level and calculate two-sided 95% confidence interval, unless otherwise specified.

### Analysis of safety

Vital signs, adverse events, laboratory tests, body weight, 12-lead electrocardiogram (ECG) and pregnancy test will be performed for the purpose of safety evaluation.

### Analysis of pharmacokinetics

Analysis of pharmacokinetics will be conducted using PKAS. During the treatment period the participants will make five visits prior to the study drug administration in the morning for a blood test. They will make another six visits after taking the morning dose to have blood samples collected. The time from the drug administration will be recorded, and the serum BPS level is to be determined. The population pharmacokinetics analysis will be conducted in addition to the pharmacokinetics analysis.

### Statistical evaluation

For the analysis of efficacy, the renal composite endpoint will be treated as an event and this evaluation will be conducted in the following steps. Step 1: Based on Cox’s proportional hazard model with the region as a covariate, contrast test will be performed on the comparison coefficient (1, -1/2, -1/2) for the placebo group, 120 μg group, and 240 μg group at two-sided 5% significance level. Step 2: If a statistical significance was observed in Step 1, pair-wise comparison between the placebo and the 120 μg groups and between the placebo group and the 240 μg group will be performed at a two-sided 5% significance level using Cox’s proportional hazard model with the region as a covariate.

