Other features of this trial are as follows:Treatment with TRK-100STP is employed, in principle, as an add-on to existing treatments. No limitation was set against concomitant ACEIs/ARBs use, although dose alternation and newly initiated prescription is restricted. Meanwhile recent evidence from large-scale clinical studies indicates that combination therapy with RAS inhibitors is not effective and also increases certain safety concerns in some of them. The add-on approach was therefore chosen in this trial, based on the observation that a new approach is required beyond RAS inhibitor-based combination therapy.This trial utilizes carefully defined eligibility criteria that allows for sufficient numbers of events while excluding slow-progressing patients. This is important because the pace of renal function deterioration varies widely among patients, especially among non-diabetic CKD patients where disease progression is sometimes very slow. Enrollment is limited to patients with SCr of 2 mg/dL or higher where an irreversible decrease in renal function is reported [23]. Clinical benefits were more clearly apparent in such patients in the previous phase II trial [22]. Participants must also have experienced progression in renal function deterioration, assessed by the slope of 1/SCr vs. time, within one year before the start of the study. These aspects of recruitment may subsequently help us define the target population likely to benefit most from intervention.The necessity of introduction of dialyses or kidney transplants were determined by the principal investigator based on medical need assessment. All endpoints including the dates of introduction of dialyses or kidney transplants, as well as cardiovascular event occurrence, were validated by an EJC whose members are third-party physicians.Patients with diabetes at pre-enrollment were excluded. The findings of several animal model studies have indicated that BPS may be effective against diabetic nephropathy [35–37]. Researchers have also reported that BPS was effective in patients with microalbuminuria [38]. However, there are several methodological difficulties in covering both diabetic and non-diabetic CKD in a single study protocol. In addition, considering there is a great unmet need for non-diabetic nephropathy treatment in Asia, we decided to prioritize and focus on non-diabetic CKD, wherein renal disorders are not modified by diabetes. As it is difficult in practice to definitively distinguish between patients with diabetic nephropathy and non-diabetic CKD patients with diabetes, all patients with diabetes at pre-enrollment are excluded.

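### The primary Cox model adjusts for region only; prespecifying baseline SCr as well would probably add some pairwise power, by an amount the article does not let us pin down

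*Protocol article*

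**What the plan says.** Protocol article, Statistical evaluation: Step 1 tests placebo against the average of the two doses, and Step 2 compares each dose with placebo. Both use a Cox "proportional hazard model with the region as a covariate". No other covariate appears.

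Study endpoints: the primary event is the first of a confirmed doubling of SCr, SCr of at least 6.0 mg/dL, dialysis or transplantation. The baseline for doubling is the "mean value of the last two measurement results during the run-in period", and SCr is measured centrally.

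Discussion: "Enrollment is limited to patients with SCr of 2 mg/dL or higher". No upper limit is given in the article; the eligibility table is in a supplementary file that is not shown. The Background reports that phase II admitted men up to 4.5 and women up to 4.0.

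Study design: the 2.5-year event rate "was 48% for the placebo group and 33% for 240 μg group". With these rates, "the number of subjects required per group is estimated at 237" ("with two-sided 5% significance level and 90% statistical power"). They are raw rates, without covariate adjustment.

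**The concern.** The endpoint combines a relative threshold (twice baseline) with an absolute one (6.0 mg/dL). Above a baseline of 3.0 mg/dL, twice baseline exceeds 6.0, so the absolute threshold always comes first and the distance to an event shrinks as baseline rises. Baseline SCr is therefore prognostic through the way the event is defined, and its value is on file for every patient. A primary model that ignores it gives up some power when patients' baselines differ widely. It also leaves chance imbalance in baseline SCr uncorrected in the estimate. At stake is efficiency in the two tests that decide the trial. Validity is not at stake.

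**Working it through.** **1. The plan's own sample size**

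Inputs (Study design): event rates 48% and 33% at 2.5 years; "assuming a 2-year-enrollment period, a 2-year follow-up period, and a 35% dropout rate at 2.5 years for each group"; two-sided 5%, 90% power.

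- Hazards, assuming exponential times: −ln(0.52)/2.5 = 0.2616; −ln(0.67)/2.5 = 0.1602; HR = 0.1602/0.2616 = 0.612. Dropout: −ln(0.65)/2.5 = 0.1723.
- Events (Schoenfeld): 4 × (1.960 + 1.282)² / (ln 0.612)² ≈ 175.
- Event probability with uniform accrual: λ/(λ+η) × [1 − (e^(−2(λ+η)) − e^(−4(λ+η))) / (2(λ+η))] = 0.434 for placebo and 0.301 for 240 μg.
- n per group = 175/(0.434 + 0.301) ≈ 238, against the stated 237.

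The figure reproduces without baseline SCr. By the same formula, power is 91.3% pairwise and 97.3% for the contrast at 250 per arm. With 892/3 ≈ 297 per arm (equal allocation assumed) it is 95.2% and 98.9%.

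**2. Distance to the SCr event**

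Fold rise needed = min(2, 6/b). Fall in 1/SCr needed = 1/b − max(1/(2b), 1/6). The article itself uses the 1/SCr slope as a measure of progression.

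| Baseline b (mg/dL) | Fold rise | Fall in 1/SCr |
|---|---|---|
| 2.0 | 2.00 | 0.250 |
| 3.0 | 2.00 | 0.167 |
| 3.5 | 1.71 | 0.119 |
| 4.0 | 1.50 | 0.083 |
| 4.5 | 1.33 | 0.056 |
| 5.0 | 1.20 | 0.033 |

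From 2.0 to 3.0 the fold rise is constant, and the fall in 1/SCr drops by a third (0.250 to 0.167). From 2.0 to 4.5 that fall shrinks 4.5-fold (0.250/0.056).

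**3. Power with and without baseline SCr**

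The prognostic strength of baseline SCr is not given, so it is varied. All simulations use 250 per arm unless stated and give both doses the 33% rate. The article states that rate for 240 μg only.

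*Proportional hazards, censoring at dropout.* Pairwise power by log HR per SD of baseline SCr:

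| Log HR per SD | Unadjusted | Adjusted |
|---|---|---|
| 0 | 91.2% | 91.3% |
| 0.3 | 91.3% | 92.0% |
| 0.5 | 90.9% | 93.8% |
| 0.8 | 90.1% | 96.0% |
| 1.0 | 92.5% | 99.1% |

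*Linear decline in 1/SCr, censoring at dropout.* Baseline uniform from 2.0 to the limit, log-slope SD 0.6 to 1.0, linear SCr term:

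| Upper limit (mg/dL) | Pairwise gain (points) | Contrast gain (points) |
|---|---|---|
| 3.0 | about 0 | about 0 |
| 4.0 | 1.4–3.2 | 1.0–1.7 |
| 4.5 | 3.6–7.2 | 1.1–2.5 |
| 5.0 | 3.8–7.2 | 1.0–2.2 |

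*Linear decline in 1/SCr under the current intention-to-treat (ITT) primary analysis.* Here 35% stop treatment and return to the untreated slope (an assumption), with log baseline SCr in the model. Pairwise gain is about 0–1 point at a limit of 3.0, 1–8 at 4.0 and 4–10 at 4.5. With about 297 per arm it is about 1–7 points. Contrast gains are smaller.

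*Smaller true effect (48% vs 38%), censoring at dropout.* Pairwise gain is 0–2 points at a limit of 3.0, 3–7 at 4.0 and 12–25 at 5.0.

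**4. Source of the gain, and type I error**

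In the linear-decline runs with censoring at dropout, the pairwise log HR moves from about −0.49 to between −0.49 and −0.70. Its SE does not fall (about 0.151 to 0.151–0.154). The gain comes from a larger conditional effect.

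With a linear SCr term and model-based SEs, type I error was 4.8–6.2% over both tests for limits 3.0 and 4.0, and 6.4–7.7% for 5.0. With log SCr under ITT it reached about 6–7% at 4.5. Part of the gain at wide ranges is therefore not real power. Robust variance and stratification were not simulated.

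**The case against.** The strongest reply is that nothing here is wrong. A region-adjusted Cox model in a randomised trial is a valid test, the sample size reproduces without baseline SCr, and adjusted supportive analyses may sit in an analysis plan that is not shown. All of that stands. It does not remove the point, because the article fixes the model of the primary test itself and leaves out a baseline value already in hand.

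Four stronger readings are tempting, and the documents do not support them:

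- *Baseline SCr is the dominant predictor.* From 2.0 to 3.0 mg/dL the criterion is the same two-fold rise. The Discussion says the pace of decline differs widely between patients. No SCr distribution or prognostic strength is given.
- *The region-only HR is biased toward 1.* The shift is non-collapsibility. The region-only HR answers a less conditional question, in line with the raw design rates. Chance imbalance is already covered by the test's error rate.
- *The omission leaves the trial underpowered.* The 237 reproduces without it. In simulations with waning after stopping, unadjusted pairwise power at 250 per arm fell to roughly 82–85%. That follows from making ITT primary without changing the sample size, and the 892 randomised offset part of it.
- *Adjustment costs nothing.* The estimand changes, a functional form must be fixed, and type I error needs watching.

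The objection is also right that the larger gains borrow the 4.5 mg/dL limit from phase II, where it applied to men only.

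**Conclusion.** The point holds as an efficiency recommendation. The region-only model is valid, but it omits a covariate that is already collected and that the endpoint makes prognostic, strongly so above 3.0 mg/dL. The expected gain in pairwise power at the planned effect is about 0–10 points at 250 per arm, somewhat less with 892 randomised, and smaller for the Step 1 contrast. It would be larger if the true effect is smaller than planned.

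The direction is consistent across the simulations wherever baseline SCr has appreciable prognostic weight. The size is uncertain. It rests on an assumed upper entry limit and baseline distribution, linear decline in 1/SCr, equal effect of both doses, and model-based SEs. Near a limit of 3.0 mg/dL there is almost nothing to gain.

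**What to change.** Before unblinding, amend Steps 1 and 2 so that the Cox model contains treatment, region and baseline SCr, using the run-in mean already defined for the endpoint. Either enter it as log SCr with a robust variance or stratify by prespecified baseline-SCr bands. Fix the form in advance, and check its type I error by simulation over the actual blinded baseline distribution. Keep the region-only model as a sensitivity analysis, and state that the primary HR is then conditional on baseline SCr.

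No new data are needed. Because the article places the primary model in the protocol, this is a protocol-level amendment, as the earlier change of primary data handling was. It is more than a wording change in the analysis plan.
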